### Study aims

The aim of this study is to develop a short-form Swedish version of the MoCA (s-MoCA-SWE) using data from Swedish stroke cohorts. The specific objectives are: (1) to identify a subgroup of MoCA items that have the potential to form the s-MoCA-SWE; (2) to determine the optimal cut-off value of s-MoCA-SWE for predicting cognitive impairment and (3) to compare the psychometric properties of s-MoCA-SWE with those of T-MoCA, NINDS-CSN and SF-MoCA.

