### Study variables

Only the variables available in both the Väststroke and EFFECTS datasets will be used. Detailed information on all variables that will be included in the study, their categories, and coding for the merged datasets are presented in online supplemental table 1.

The MoCA is a valid and reliable instrument for cognitive screening in the acute and subacute phases of stroke.^8–10^ The total MoCA score ranges between 0 and 30 points (p); 1 p for a maximum of 12 years of education can be added to the total score. A score of ≤25 p indicates cognitive impairment.^8^ MoCA items were registered in the datasets as follows:

Orientation (range, 0–6 p).Delayed recall (range, 0–5 p).Visuospatial/executive functions (range, 0–5 p): trial (1 p)+cube (1 p)+clock (3 p).Naming of three animals (range, 0–3 p).Digit span, two tasks (range, 0–2 p).Repetition of two sentences (range, 0–2 p).Categories, two tasks (range, 0–2 p).Serial 7 (range, 0–3 p).Fluency (range, 0–1 p).Tap on A (range, 0–1 p).

Stroke severity at onset was assessed using the National Institutes of Health Stroke Scale (NIHSS).^28^ The NIHSS comprises 15 items with varying score ranges per item. The total NIHSS score is 0–42 p, with a higher score indicating a more severe stroke.^28^

Reperfusion treatment will be categorised as both thrombolysis and thrombectomy, only thrombolysis or only thrombectomy.

Information about a previous stroke and/or TIA was recorded (yes, no or unknown). The Väststroke register comprises patients with a first-ever stroke, however, patients with previous TIA were included. In the EFFECTS study, patients could have a prior stroke and/or TIA, and these two conditions could not be distinguished.

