#### Aggregated variables

The T-MoCA is a short version of the MoCA that is based on the following items: delayed recall, digit span, list letters, serial 7, sentence repetition, fluency, abstraction and orientation.^14^ The total T-MoCA score is 22 p. The reported threshold for impaired cognition is ≤18 p.^14^

The NINDS-CSN is based on items such as delayed recall, fluency, and orientation.^15 17–19^ The total NINDS-CSN score is 12 p. The suggested thresholds for impaired cognition are ≤9 p,^13 15^ ≤10 p^16^ and ≤6 p.^17 29^

The SF-MoCA is based on items such as delayed recall, serial 7 and orientation.^11 12^ The total SF-MoCA score is 14 p, and a cut-off of ≤8 p has been suggested as an indicator for impaired cognition.^11 12^

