The decision between the set of MoCA items derived from exploratory factor analysis and that derived from the boosted regression tree algorithm will be made by applying binary logistic regression analysis. The sets will be entered as independent variables and tested using different regression models. The dependent variable will be dichotomised MoCA (≤25 p for impaired cognition).^8 33^ The s-MoCA-SWE version with the highest sensitivity and classification accuracy for cognitive impairment will be analysed in objective 2.

#### Objective 2

To find the optimal cut-off value of s-MoCA-SWE for classifying patients with and without cognitive impairment, binary logistic regression analysis will be performed. The MoCA cut-off of ≤25 p for impaired cognition will be the reference output,^8 33^ and the s-MoCA-SWE full score will be the independent variable. The cut-off value of s-MoCA-SWE will be chosen based on its good sensitivity for identifying patients with cognitive impairment.

#### Objective 3

Four cross-tables will be evaluated. The reference variable will be dichotomised MoCA (≤25 p for impaired cognition).^8 33^ The index variables will be dichotomised s-MoCA-SWE (according to the results from Objective 2), T-MoCA (≤18 p for impaired cognition),^14^ NINDS-CSN (≤9 p for impaired cognition)^13 15^ and SF-MoCA (≤8 p for impaired cognition).^11 12^ The psychometric measurements of sensitivity, specificity, positive predictive value, negative predictive value and Youden’s index with 95% CI will be evaluated.

Receiving operating characteristic curve analysis will be performed. The full scores of s-MoCA-SWE, T-MoCA, NINDS-CSN and SF-MoCA will be entered as test variables, and the dichotomised MoCA (≤25 p for impaired cognition) will be entered as the state variable.^8 33^ The areas under the curve will be interpreted as follows: 0.7–0.9, moderate accuracy and 0.5–0.7, low accuracy.^34^

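### Every short form is part of the MoCA that defines impairment, so Objective 3 measures agreement with the full MoCA, and SF-MoCA specificity and PPV are 100% by arithmetic

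*Protocol article*

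**What the plan says.** Under Study aims, the second objective is "to determine the optimal cut-off value of s-MoCA-SWE for predicting cognitive impairment". The third is to compare the new form with T-MoCA, NINDS-CSN and SF-MoCA.

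Under Statistics, Objective 3, the cross-tables are defined by "The reference variable will be dichotomised MoCA (≤25 p for impaired cognition". The SF-MoCA index is set by "and SF-MoCA (≤8 p for impaired cognition", with T-MoCA cut at ≤18 and NINDS-CSN at ≤9. Sensitivity, specificity, PPV, NPV and Youden's index are to be given with 95% confidence intervals. In the ROC analysis, "the dichotomised MoCA (≤25 p for impaired cognition) will be entered as the state variable", and the AUC bands are read as grades of accuracy. Objectives 1 and 2 use the same reference to choose between the item sets and to set the s-MoCA-SWE cut-off.

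Under Aggregated variables, "The total SF-MoCA score is 14 p, and a cut-off of ≤8 p has been suggested as an indicator for impaired cognition". Under Study variables, the full score is described thus: "The total MoCA score ranges between 0 and 30 points (p); 1 p for a maximum of 12 years of education can be added". No cognitive reference outside the MoCA is described. The listed limitations mention retrospective registry data and missing MoCA values, but not the overlap between index and reference.

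**The concern.** Index and reference are not separate measurements. A patient who loses points on a short form loses the same points on the total that decides whether that patient is impaired. This has two consequences.

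First, where a cut-off lies far enough below the form's maximum, a positive short form forces a positive reference. Part of the cross-table is then known before any data are seen, yet the plan would estimate it with a confidence interval and set it beside the other forms.

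Second, the remaining measures, including the AUC, answer how well a part reproduces the whole. Objective 2 and the AUC labels present that as accuracy for cognitive impairment. The form is meant for screening in acute and subacute stroke, so clinicians could take the figures as detection rates against a separate standard.

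**Working it through.** **Inputs.** From Study variables: "Orientation (range, 0–6 p).Delayed recall (range, 0–5 p" and "Serial 7 (range, 0–3 p". The other item maxima are visuospatial/executive 5, naming 3, digit span 2, repetition 2, categories 2, fluency 1 and tapping 1. Form content and published cut-offs are in Aggregated variables; the cut-offs used are in Objective 3.

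**Reproducing the plan's own totals.**
- Full MoCA: 6 + 5 + 5 + 3 + 2 + 2 + 2 + 3 + 1 + 1 = 30.
- SF-MoCA (delayed recall, serial 7, orientation): 5 + 3 + 6 = 14, as stated.
- NINDS-CSN (delayed recall, fluency, orientation): 5 + 1 + 6 = 12, as stated.
- T-MoCA (all but visuospatial/executive and naming): 30 − 5 − 3 = 22, as stated.

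**Bound.** If a form has maximum M and is positive at ≤ c, the highest possible full MoCA is c + (30 − M). Add 1 if the reference total includes the education point.

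| Form and planned cut-off | Highest full MoCA when positive | With education point | False positive possible? |
|---|---|---|---|
| SF-MoCA ≤8 of 14 | 8 + 16 = 24 | 25 | No, either way |
| T-MoCA ≤18 of 22 | 18 + 8 = 26 | 27 | Yes |
| NINDS-CSN ≤9 of 12 | 9 + 18 = 27 | 28 | Yes |

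**Enumeration.** There are 435,456 possible item-score patterns. Of the 300,672 that are SF-MoCA positive, none has a full MoCA above 25, with or without the point. T-MoCA has 234 such patterns without the point and 1,152 with it; NINDS-CSN has 65 and 328. These are counts of possible patterns, not of patients.

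**Consequence for SF-MoCA.** With no false positives, specificity = TN/(TN + 0) = 1, PPV = TP/(TP + 0) = 1, and Youden's index = sensitivity + 1 − 1 = sensitivity. This needs only at least one SF-MoCA-positive patient and one patient with MoCA above 25.

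**General threshold, relevant to s-MoCA-SWE.** Specificity is fixed when c + 30 − M ≤ 25, that is c ≤ M − 5, if the reference excludes the education point. If it includes the point, c + 31 − M ≤ 25, that is c ≤ M − 6. SF-MoCA ≤8 is M − 6, so it is fixed under both.

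**Illustration of the AUC effect (assumed inputs).** 200,000 patients were simulated from a one-factor model, scored point by point. Assumed pass rates: orientation 0.92, recall 0.50, visuospatial 0.72, naming 0.93, digit span 0.85, repetition 0.75, categories 0.75, serial 7 0.82, fluency 0.50, tapping 0.90. Each cell gives the AUC against the containing MoCA ≤25, then against ≤25 on a parallel MoCA that shares only the latent ability.

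| Common loading | T-MoCA | NINDS-CSN | SF-MoCA |
|---|---|---|---|
| 0 | 0.949 → 0.503 | 0.854 → 0.503 | 0.862 → 0.504 |
| 0.3 | 0.965 → 0.746 | 0.895 → 0.703 | 0.902 → 0.712 |
| 0.5 | 0.980 → 0.866 | 0.935 → 0.829 | 0.939 → 0.835 |
| 0.7 | 0.990 → 0.932 | 0.968 → 0.910 | 0.968 → 0.912 |

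The gap runs from about 0.06 to about 0.45. SF-MoCA specificity and PPV are 1.000 against the containing MoCA in every row; against the parallel one they are 0.912–0.994 and 0.882–0.989.

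**The case against.** The study sets out to build a short form of the MoCA, and it declares the full MoCA ≤25 as the reference at each step. Reproducing the parent classification is a legitimate question, and against that target no AUC is inflated. This stands. The analysis can stay; what needs changing is the description of what it shows and the use of values that cannot vary.

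The size of the AUC effect is also open. The largest gap needs items that share no trait, whereas the plan expects correlated items (it looks for a significant Bartlett's test and a Kaiser-Meyer-Olkin value above 0.7). At loading 0.7 the forms still reach 0.91–0.93 against a separate parallel MoCA. This stands too. A reader might infer that the planned AUCs reflect overlap and nothing else, or that a definite amount can be subtracted; the document supports neither.

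A reader might also infer that any form cut at its maximum minus 5 or lower always has 100% specificity. That fails if the education point is in the reference total: a loss of exactly 5 points then gives 26, which is not impaired. For example, T-MoCA ≤17 would have 450 false-positive patterns and NINDS-CSN ≤7 would have 11. Neither is a planned cut-off.

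**Conclusion.** The point holds in a limited form. It is exact for SF-MoCA ≤8: specificity and PPV are 100% and Youden's index equals sensitivity for any data, whether or not the education point is counted. T-MoCA ≤18 and NINDS-CSN ≤9 are constrained by the same overlap but remain estimable. Without the education point, a T-MoCA false positive needs exactly 18 on the form and all 8 remaining points; with the point, a few more combinations qualify.

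The other Objective 3 measures and the AUCs are valid as agreement with the full-MoCA classification. They do not show accuracy for cognitive impairment judged independently. Relative to such a reference, overlap raises them, but the amount cannot be derived from the document. The 0.06 to 0.45 range rests on assumed item difficulties and loadings and is illustrative only. The point does not show that the short forms lack diagnostic value or that the study should not be run.

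**What to change.** 1. Restate Objectives 2 and 3, the AUC interpretation and the planned conclusions as agreement with full MoCA ≤25, and add the index–reference overlap to the limitations.
2. State that SF-MoCA ≤8 specificity and PPV are 100% by construction. A note to the table is enough, but do not rank the forms on these values or on a Youden's index built from them.
3. State whether the reference total includes the education point. Apply item 2 to s-MoCA-SWE if its chosen cut-off is at maximum − 5 or lower (point excluded) or maximum − 6 or lower (point included).
4. Optional sensitivity analysis: relate each form to the MoCA score from the items it does not contain, or set its AUC against those of item subsets with the same maximum score. The remaining items differ by form (8 points outside T-MoCA, 16 outside SF-MoCA, 18 outside NINDS-CSN), so the first is not a like-for-like ranking.

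Items 1 to 3 are wording and need no new data; item 4 is a short additional analysis. The price is that the headline accuracy claims become less favourable.

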## Introduction

Cognitive impairment, a common sequela of stroke, has been defined as a new cognitive deficit that develops in the first 3 months after stroke and cannot be explained by other conditions or diseases.^1^ Cognitive impairment is a consequence of complex interactions between age, education and injury size and location.^2^ The prevalence of cognitive impairment in the first 3 weeks after stroke can vary between 55% and 59% depending on the time of assessment and the assessment instruments.^3 4^ Previous studies have shown that cognitive impairment after stroke is associated with higher mortality and long-term disability.^5^ Thus, early identification of cognitive impairments after stroke is important for planning individually tailored rehabilitation.

Comprehensive cognitive assessments in acute stroke units can be time and resource demanding for patients as well as for healthcare professionals. Therefore, the use of short screening tools for cognitive impairment is recommended.^6 7^ The Montreal Cognitive Assessment (MoCA) is frequently used to screen cognitive function.^7^ The MoCA targets cognitive domains such as visuospatial ability, executive function, attention, concentration, working memory, language, short-term memory and orientation.^8^ It has a good sensitivity for detecting poststroke cognitive impairment.^9 10^ To make cognitive screenings time effective, several short forms of the MoCA have been developed and tested in recent years, including a telephone version of the MoCA (T-MoCA), a short version of the MoCA that has been designed by the National Institute of Neurological Disorders and Stroke and the Canadian Stroke Network (NINDS-CSN, 5 min protocol) and the short-form MoCA (SF-MoCA).^11–19^ Different cutoffs for impaired cognition have been reported for the MoCA as well as its short forms.^11 12 15 17–20^ None of the available short forms have been developed or validated in a Swedish sample of patients with stroke.

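### The Objective 3 cross-tables set one short form at a cut-off tuned in this sample beside three held at imported cut-offs, so they are not like-for-like, chiefly for SF-MoCA ≤8

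*Protocol article*

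**What the plan says.** The relevant text is in the protocol article, under Statistics (Objectives 1 to 3), Aggregated variables and Introduction.

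- **Item set (end of Objective 1).** Two candidate sets are compared against MoCA ≤25: "The s-MoCA-SWE version with the highest sensitivity and classification accuracy for cognitive impairment will be analysed in objective 2".
- **New cut-off (Objective 2).** With MoCA ≤25 again as reference: "The cut-off value of s-MoCA-SWE will be chosen based on its good sensitivity for identifying patients with cognitive impairment". No numeric target and no floor for specificity is given.
- **Cross-tables (Objective 3).** "The index variables will be dichotomised s-MoCA-SWE (according to the results from Objective 2), T-MoCA (≤18 p for impaired cognition", followed by "NINDS-CSN (≤9 p for impaired cognition" and "SF-MoCA (≤8 p for impaired cognition". Sensitivity, specificity, PPV, NPV and Youden's index are to be evaluated with 95% CIs.
- **ROC analysis (Objective 3).** The full scores of all four forms are compared against MoCA ≤25 by area under the curve.
- **Published thresholds.** Aggregated variables lists three for NINDS-CSN: "The suggested thresholds for impaired cognition are ≤9 p", then ≤10 and ≤6. Objective 3 uses only the first.
- **Known variation.** The Introduction states: "Different cutoffs for impaired cognition have been reported for the MoCA as well as its short forms". It adds that MoCA items can work differently across cultures and that this extends to short forms.

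**The concern.** A cross-table at a fixed cut-off measures two things together: how well the items separate patients, and where the line is drawn. Here the line for one form is drawn in this sample, against this reference, with sensitivity as the aim. The lines for the other three come from other samples. The protocol's own case for cultural validation is a reason to doubt that imported cut-offs transfer.

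At stake is how the sensitivity, NPV and Youden rows are read. These are the figures a clinician would use to choose a screening form, and a gap caused by calibration could be taken as evidence that the new item set is better.

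**Working it through.** The plan states no expected accuracy, sample size or power for Objective 3, so there is no figure of its own to reproduce. The check has an arithmetic part, which needs no assumptions, and an illustrative part.

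**1. Arithmetic from the item ranges (Study variables) and the cut-offs (Objective 3)**

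Maxima: SF-MoCA = recall 5 + serial 7 3 + orientation 6 = 14. NINDS-CSN = 5 + fluency 1 + 6 = 12. T-MoCA = 5 + 2 + 1 + 3 + 2 + 1 + 2 + 6 = 22, as the plan has it ("The total T-MoCA score is 22 p"). The MoCA items sum to 30. All match the stated totals.

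| Form | Cut-off / maximum | Share | Points lost to be called impaired |
|---|---|---|---|
| MoCA (reference) | 25/30 | 83% | 5 |
| T-MoCA | 18/22 | 82% | 4 |
| NINDS-CSN | 9/12 | 75% | 3 |
| SF-MoCA | 8/14 | 57% | 6 |

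SF-MoCA ≤8 means at least 14 − 8 = 6 points lost. All its items are MoCA items, so raw MoCA ≤ 30 − 6 = 24, or ≤ 25 if the education point is added. Every SF-MoCA positive is therefore a reference positive, and specificity and PPV are 100% whatever the data show. Conversely, a reference-positive patient with raw MoCA 25 has lost only 5 points and must be missed. So must any impaired patient who loses fewer than 6 points on recall, serial 7 and orientation.

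**2. Illustration of size (assumed data)**

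Item scores were simulated for 200,000 patients in each of 8 scenarios, from a one-factor logistic model with item-level noise. Item difficulties, discrimination (0.8 or 1.2) and mean ability (0.3 to 1.2) are assumptions. The share with MoCA ≤25 ran from 31% to 70%; the Introduction quotes 55–59% for cognitive impairment. No education point was added. Ranges are over the 8 scenarios; Youden = sensitivity + specificity − 1.

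| Form and cut-off | Sensitivity | Specificity | Youden |
|---|---|---|---|
| SF-MoCA ≤8 (planned) | 0.11–0.31 | 1.00 | 0.11–0.31 |
| SF-MoCA ≤11 (its Youden optimum) | 0.76–0.85 | 0.86–0.93 | 0.65–0.75 |
| NINDS-CSN ≤9 (planned, and its Youden optimum) | 0.76–0.85 | 0.85–0.93 | 0.64–0.74 |
| NINDS-CSN ≤10 | 0.94–0.96 | 0.53–0.73 | 0.49–0.68 |
| T-MoCA ≤18 (planned, and its Youden optimum) | 0.91–0.95 | 0.88–0.95 | 0.82–0.86 |

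Scenario by scenario, re-cutting SF-MoCA alone adds 0.44 to 0.55 to Youden. A separate simulation (57% impaired, common loading 0.6) gave sensitivity and Youden 0.39 at ≤8, and sensitivity 0.86, specificity 0.89 and Youden 0.75 at ≤11, a gain of 0.75 − 0.39 = 0.36. The size thus depends on the assumptions; the direction does not.

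SF-MoCA and NINDS-CSN show the effect most clearly. In the 8 scenarios their AUCs differ by at most 0.005 (0.902–0.941 against 0.899–0.937). At the planned cut-offs their Youden indices are 0.11–0.31 and 0.64–0.74. Two forms with nearly equal discrimination look very different because of where each is cut.

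**3. Is this over-fitting of one cut-off?**

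No. Tuning one Youden cut-off on half the data and testing it on the other half gave mean optimism of 0.009 at n = 300 and about 0 at n = 1000 and n = 3000. The problem is unequal calibration.

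**The case against.** Four points on the other side have weight.

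- **The AUC analysis.** It uses no cut-off and one reference for all four forms, so it largely supplies the item-content comparison that the cross-tables cannot. This stands as partial mitigation. It does not repair the sensitivity, NPV and Youden tables, and it keeps a tilt of its own because the s-MoCA-SWE items are chosen against the same reference in the same data source.
- **Published cut-offs answer a fair question.** They show how existing forms perform as now used, and a new form has no published cut-off to import. This stands, and is why that table should be kept.
- **One NINDS-CSN threshold fixed in advance.** This prevents a choice after the fact, and ≤9 is not the threshold that most flatters the new form: ≤6 had sensitivity of only 0.09–0.27 in the 8 scenarios. This also stands.
- **The study is called exploratory.** No superiority test or margin is stated for Objective 3, which lowers the stakes.

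A reader might go further and infer that s-MoCA-SWE wins largely by design. The documents do not support that. The AUCs are untouched by cut-offs. T-MoCA ≤18 is nearly proportional to MoCA ≤25 and keeps 22 of the 30 points. In the simulations its Youden index (0.82–0.86) exceeded that of a hypothetical 13-point new form (0.70–0.79) tuned on Youden. A cut-off chosen for sensitivity may also cost the new form specificity and PPV, where SF-MoCA is at 100%. Nor can anyone yet say what share of a future gap would be due to tuning, because the s-MoCA-SWE items are not chosen.

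**Conclusion.** The concern holds for the threshold-based half of Objective 3. The cross-tables compare a form calibrated to this sample with three that are not. The effect differs by form:

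- **SF-MoCA ≤8:** serious. Specificity of 100% and limited sensitivity follow from the item ranges alone.
- **NINDS-CSN ≤9:** affected on sensitivity, the criterion used for the new form. Moving to ≤10 raised it from 0.76–0.85 to 0.94–0.96 in the 8 scenarios, at a clear cost in specificity. On Youden there was no handicap.
- **T-MoCA ≤18:** little affected.

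The 57% against 83% contrast and the 100% specificity need no assumption. All simulated sizes rest on assumed item difficulties and are illustrative only. This is a cheap and worthwhile improvement, not a flaw that invalidates the objective.

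**What to change.** Derive the cut-off for all four forms by the same pre-stated rule in the same data, or compare sensitivity at a matched specificity. The rule needs a stated target, since Objective 2 now gives none. Use that table together with the AUC comparison for any claim about relative performance. Report the published cut-offs in a companion table, labelled as performance in current use; all three listed NINDS-CSN thresholds could be shown there.

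The item scores are already in both datasets, so the cost is one extra table. The downside is that the apparent advantage of s-MoCA-SWE may shrink.
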